### Modification

#### Stop criteria and dose changes

Considering that unstable newborns (i.e. after anesthesia induction) have shown a high risk of adverse events (hypotension and bradycardia) due to propranolol administration, whenever surgery and/or anesthesia are indicated, the discontinuation of the propranolol eye micro-drops treatment is recommended at least 24 h before.

Newborns in whom propranolol administration will be temporarily suspended for more than two doses, with the exception of a temporary suspension before surgery will be excluded from the study.

In the case of a severe adverse event (bradycardia, bronchospasm, severe hypotension or severe local signs) due to propranolol eye micro-drops therapy, the treatment will be promptly stopped and the newborn will be excluded from the study. The concentration of propranolol will be measured on dried blood spots to verify the relationship between the adverse event that occurred and the plasmatic levels of propranolol. Moreover, after the first adverse event, the study could be restarted reducing the propranolol eye drops dosage to two micro-drops of 6 μL 0.2% propranolol solution administered four times daily in each eye. An additional enrolment phase will be opened and will be based on a new study population not including newborns previously treated.

Similarly, the study could be restarted increasing the concentration of propranolol eye drops solution up to 0.3% in case of treatment failure in terms of efficacy during the first stage of the study, if plasma propranolol concentrations are below the cut off of 20 ng/ml.

The outcomes of infants who develop adverse effects to propranolol will be reported to Pharmacovigilance Center and then published.

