### Experimental plan

The study was planned as a Simon optimal two-stage design [65] (Fig. 1), under the hypothesis that propranolol 0.2% eye micro-drops treatment decreases the incidence of ROP progression to stage 2 or 3 with plus by at least 50%. From a first analysis of the historical cohort of neonates the incidence was found to be 19%. A second and deeper analysis showed that the incidence was likely somewhat higher (24.5%) (Table 2). The study size adopted is based on the first and more conservative estimate. Therefore, considering an alpha error of 0.05 and a power of 80%, the treatment should be considered failed if:-at least 6 cases of failure (a progression of ROP to stage 2 with plus or 3 with plus) is observed in the first 37 newborns enrolled;-at least 13 out of 96 newborns enrolled show a treatment failure (a progression of ROP to stage 2 with plus or 3 with plus).

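### Treated infants can be excluded from the study after enrolment, yet both decision rules count all infants enrolled; unless this is reconciled, the false-positive rate can exceed 5%

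*Protocol article*

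**What the plan says.** Two rules in the protocol article, under Stop criteria and dose changes, act after treatment has begun.

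- Infants whose drops are "temporarily suspended for more than two doses, with the exception of a temporary suspension before surgery will be excluded from the study".
- After a severe adverse event attributed to the drops, "the treatment will be promptly stopped and the newborn will be excluded from the study". Stopping treatment and leaving the study are named as two separate steps.

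The Experimental plan sets the decision rule "considering an alpha error of 0.05 and a power of 80"%. The hypothesis is that treatment "decreases the incidence of ROP progression to stage 2 or 3 with plus by at least 50"%. The treatment has failed if a count of six or more failures "is observed in the first 37 newborns enrolled", or if "at least 13 out of 96 newborns enrolled show a treatment failure". On the rate used for sizing, the article says: "From a first analysis of the historical cohort of neonates the incidence was found to be 19"%. A later analysis of the same cohort gave 24.5% (58 of 237), but the design was left at 19%.

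The article does not say whether excluded infants are followed for the primary endpoint, whether they are replaced, or how they enter the 37 and the 96.

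**The concern.** In a single-arm trial the historical rate is the only comparator, so the trial infants should be selected in the same way as the historical ones. Under Preliminary analysis, the 237 historical infants were selected only on the trial's enrolment criteria: 3 of the 248 were dropped for aggressive posterior disease and 8 for stage 2 or worse at first examination. Nothing that happened later removed anyone. In the trial, later events can remove an infant, and the dose threshold is low: three suspended doses out of up to 4 × 90 = 360.

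The article makes it plausible that the infants removed are at higher risk. Its section on oral propranolol reports serious adverse events in unstable infants, mainly alongside conditions such as sepsis. Its Background names sepsis, respiratory failure, intraventricular haemorrhage and necrotizing enterocolitis as contributing to ROP.

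If failures in excluded infants are not counted, the observed rate can drop below a boundary without any drug effect. Both decisions are exposed: whether to go on after 37 infants, and whether to call the treatment effective after 96.

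**Working it through.** **Inputs from the Experimental plan.** Null failure rate 0.19; alternative 0.19 × 0.5 = 0.095; continue with at most 5 failures in 37; effective with at most 12 in 96, so the second stage has 96 − 37 = 59 infants.

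**Assumed, because the article gives no figure.** The share of enrolled infants excluded, e, and the progression risk of excluded relative to retained infants, RR.

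**Step 1: reproduce the design.** The probability of declaring the treatment effective at failure rate p is

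S(p) = Σ (x = 0 to 5) P[Bin(37, p) = x] × P[Bin(59, p) ≤ 12 − x].

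S(0.19) = 0.0493 and S(0.095) = 0.802. An exhaustive search for the Simon optimal design at these inputs returns the same 37 and 96 with the same cut-offs. The plan's figures are therefore right when every enrolled infant is counted, but only 0.0007 of the 0.05 is left over.

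**Step 2: model the exclusion with no drug effect.** Keep the rate over all enrolled infants at p. Since p = (1 − e)·r + e·RR·r, the rate among retained infants is r = p / (1 − e + e·RR). Two readings follow.

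- Replaced: 37 and 96 are counts of retained infants, and the error is S(r).
- Kept as non-failures: 37 and 96 are counts of enrolled infants and no failure in an excluded infant is counted, so the error is S((1 − e)·r).

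Example with e = 0.05 and RR = 2: r = 0.19/1.05 = 0.1810, S = 0.075. Then 0.95 × 0.1810 = 0.1719, S = 0.111.

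**Step 3: false-positive rate at an untreated rate of 19%.**

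| Excluded | Reading | RR 0.5 | RR 1 | RR 2 | RR 3 |
|---|---|---|---|---|---|
| 2% | replaced | 4.5% | 4.9% | 5.9% | 6.9% |
| 2% | kept as non-failures | 5.4% | 5.9% | 7.0% | 8.2% |
| 5% | replaced | 3.9% | 4.9% | 7.5% | 10.7% |
| 5% | kept as non-failures | 6.2% | 7.7% | 11.1% | 15.1% |
| 10% | replaced | 3.0% | 4.9% | 10.7% | 18.7% |
| 10% | kept as non-failures | 7.8% | 11.5% | 20.7% | 31.4% |

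With replacement, the error exceeds 5% only if excluded infants are at higher risk. With non-counting, it exceeds 5% in every cell. The second reading is an upper bound, because an infant who progresses before the suspension might already have been counted.

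**Step 4: untreated rate of 24.5%.** Without exclusions S(0.245) = 0.2%. With 10% excluded at RR 2 the error is 0.9% (replaced) or 2.9% (kept as non-failures). It takes more to pass 5%: 10% excluded at RR 3 gives 2.4% or 6.6%.

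**The case against.** The article never says that excluded infants leave the failure count. Both rules are worded over infants enrolled, which read literally keeps them in, and guideline eye examinations are planned for infants in the study. Analysis sets often sit in a fuller document. This stands as far as it goes: removal from the count is an inference. But the exclusion and the counting rule are both stated in this article, and an infant excluded from the study can supply an outcome to a count over all enrolled infants only if followed. The two sections need reconciling on any reading.

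A reader might infer that the rule strips out the sickest infants and that the 5% error is certainly lost. The documents do not support that. Suspensions before surgery are exempt, the adverse-event rule covers only events due to the drops, and the article reports no adverse effects with the 0.1% drops, though that was a lower concentration. Nothing in the article links a suspension of more than two doses to progression. With replacement and equal risk the error stays at 4.9%, and with lower-risk exclusions it falls.

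It is also fair to say that tolerability failures are not hidden altogether: outcomes of infants with adverse effects are to be reported to pharmacovigilance and published, and adverse events due to the drops are a secondary endpoint. That does not place those infants in the 37 or the 96, and it does not cover infants excluded for interrupted dosing alone.

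**Conclusion.** The point holds as a conflict between two stated rules, with a conditional effect on the false-positive rate. At the 19% rate on which the trial was sized, and for RR 1 to 2, the error is 4.9–5.9% (replaced) or 5.9–7.0% (kept as non-failures) with 2% excluded, 4.9–7.5% or 7.7–11.1% with 5%, and 4.9–10.7% or 11.5–20.7% with 10%. The exclusion share and RR are assumptions; higher risk among excluded infants is plausible from the article but not quantified there. If the untreated rate is really 24.5%, up to 10% excluded at RR 2 keeps the error at 2.9% or less. It should be settled before the first decision at 37 infants, because it bears on both decisions and the design has no room to absorb uncounted failures.

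**What to change.** Amend the text so that every infant who receives at least one dose stays under the planned guideline eye examinations to the endpoint and is counted in the 37 and the 96. Such an infant is a failure if progression to stage 2 or 3 with plus is observed, whether or not drops were interrupted or stopped. Use the present exclusion only to define a per-protocol sensitivity set. The clinical rules on suspending or stopping drops are not touched.

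The sample size and cut-offs stay as they are. The error returns to 4.9%, and power is 80.2% provided the rate over all treated infants still reaches 9.5%. The cost is a short amendment and a slight dilution of the on-treatment effect; no examination is added beyond those already planned.

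Counting every excluded infant as a failure would be a poor substitute. The failure rate becomes p(1 − e) + e, which holds the error below 5% but cuts power to 62.5% with 2% excluded, 33.5% with 5% and 6.1% with 10%.

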#### Efficacy and safety of oral propranolol

The studies in the OIR model provided a considerable amount of results which strongly indicate that β2-AR blockade may play a significant action against hypoxia-induced retinal neovascularization. This evidence prompted an interest in exploring the possibility that the administration of propranolol may not only be used to treat IH but also be of help in the treatment of ROP. A randomized controlled trial [56] was performed to verify the efficacy and safety of oral propranolol in preterm newborns (GA < 32 weeks) with ROP stage 2 without plus in zone II [57]. Oral propranolol significantly decreased ROP progression to both stage 3 and stage 3 with plus, and none of treated newborns progressed to stage 4. The number of newborns who underwent laser photocoagulation or bevacizumab administration was significantly lower in the treated group [56]. These data are consistent with those reported by other authors [58–60]. Despite propranolol being generally safe and well tolerated in infancy, serious adverse events have been reported in unstable preterm newborns, mainly in conjunction with other conditions, such as sepsis, anesthesia or tracheal stimulation [56]. In these patients receiving the lower dose of 1 mg/kg/day, mean propranolol plasma concentration was around 20 ng/mL. Considering that pharmacological effects of β-blockers are usually related to the plasma concentrations, it appears prudent to avoid in future clinical trials propranolol concentrations higher than 20 ng/mL, that was considered a sort of safe cut-off value [56]. Although propranolol is effective in counteracting ROP progression [56, 58–60], the incidence of adverse events indicates that systemic administration is not sufficiently safe in preterm newborns [56]. Recently, also prophylactic propranolol administered on seventh day of life showed a decreasing trend in the incidence of ROP, need for laser therapy, and treatment with anti-VEGF [61].

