#### Safety and efficacy of propranolol 0.1% eye micro-drops in newborns

Recently an open-label, trial was performed to evaluate the safety and efficacy of propranolol 0.1% eye micro-drops in preterm newborns with stage 2 ROP without plus [64]. The study was planned according to the Simon optimal two-stage design for phase II clinical trials and it was discontinued before starting the second stage since the number of failures was above the set threshold. Even though the objective to move to the second stage was not reached, the percentage of ROP progression (around 26%) was substantially similar to that obtained after oral propranolol administration. Nevertheless, no adverse effects were observed and propranolol plasma levels were significantly lower than those measured after oral administration (consistently below the cut-off value of 20 ng/mL). Therefore, treatment with propranolol 0.1% eye micro-drops seems to be safe and well tolerated in preterm newborns, but not sufficiently effective in reducing ROP progression.

Further research is then required to identify the optimal dose and schedule of topical propranolol therapy for ROP.

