### Intervention

All enrolled newborns will receive propranolol as ophthalmic solution (0.2%). Three micro-drops of 6 μL propranolol solution (= 6 μg propranolol/μ-drops) will be topically applied four times daily (every 6 h) in each eye with a calibrated pipette. After propranolol administration, the nasolacrimal duct will be carefully compressed for 1 min in order to decrease the percentage of drug absorbed by the conjunctival and nasal vessels. The treatment will be started as soon as the diagnosis of stage 1 ROP without plus is confirmed and will be continued until the complete development of retinal vascularization, but for no longer than 90 days. However, ophthalmologic exams will also be performed after this period to exclude possible rebound phenomenon. In these cases, propranolol eye micro-drops treatment will be resumed until retinal vascularization is completed.

The ophthalmologic approach for newborns enrolled in the study will be in accordance with the guidelines adopted by the ETROP Cooperative Group and the AAP/AAO/AAPOS guidelines [3, 66, 67]. The RetCam Imaging System will be systematically used by ophthalmologists to evaluate ROP evolution.

Eye drops will be prepared sterilely by diluting propranolol hydrochloride powder (ACEF, Fiorenzuola d’Arda, Piacenza, Italy), in sterile water for injection at a concentration of 2%. Then, the propranolol 0.2% solution will be obtained in a horizontal laminar flow hood adding 9 ml of saline solution to 1 ml of propranolol 2% preparation.

Newborns with ROP who progressed to stage 2 plus or stage 3 plus will be treated with laser photocoagulation or intravitreal anti-VEGF (bevacizumab) administration. The ophthalmologists will choose the treatment they will consider most appropriate.

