## Methods: Data collection, management, analysis

### Data collection methods

All data will be registered in specific case report form including neonatal demographic data, prenatal and perinatal history and morbidity profiles of both mother and newborn. Hemodynamic parameters, diuresis and respiratory parameters will be continuously monitored during the first 3 weeks of treatment. Biochemical parameters, such as a complete blood count, serum electrolytes levels, renal and liver function tests will be measured before starting treatment (T0) and once a week for the first 3 weeks of treatment (T7, T14, and T21). Electrocardiogram and echocardiogram will be performed before starting treatment and once a week for 3 weeks of treatment. Any drugs that are concomitantly administered and procedures performed will be recorded.

To investigate the safety of propranolol 0.2% eye micro-drops treatment, the concentration of propranolol will be measured on dried blood spots using the liquid-chromatography tandem-mass spectrometry test [68, 69] at the steady state on the 10th day of treatment, before administering therapy (T0), after 2 (T2), 4 (T4) and 6 h (T6). Additionally, parents will be asked to consent to us taking and storing 0.3 ml of plasma.

The stage of ROP disease should be established by complete ophthalmological evaluations, planned according to ROP Guidelines [3, 66, 67], also considering the progression and the severity of ROP. The ophthalmologic exam should verify the absence of local adverse events due to the propranolol eye micro-drops treatment, as well as analyze corneal and vitreous transparencies, lens opacity, and regression of vessels in the tunica vasculosa lentis. The ROP progression will be monitored by indirect ophthalmoscopy using a 20D and 28D lens. The RetCam Imaging System will be systematically used by ophthalmologists to evaluate ROP evolution.

The timeline of the study is reported in Additional file 1.

All the adverse effects will be notified to the qualified responsible of pharmacovigilance, using the specified report form.

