**Fig. 1 Fig1:**
[figure not shown]
Simon optimal two-stage design for phase II clinical trials

At the end of the study, if the overall cases of failure are less than 13 out of 96 newborns, the treatment with propranolol 0.2% eye drops will be considered effective in decreasing the rate of ROP progression to stage 2 or 3 with plus.

Additionally, considering the serious adverse effects observed in newborns receiving oral propranolol with plasma concentrations around 20 ng/mL, this value is currently considered a sort of safe cut-off value [55]. For this reason, if the mean propranolol plasma concentration will be less than 20 ng/ml, as expected, the treatment with propranolol eye drops should be considered safe, being unable to cause high plasma levels of propranolol.

The 96 preterm newborns will be enrolled approximately in 2–3 years. The enrokllment will be competitive: the individual centers participating in the trial will not have a predetermined number of patients to recruit, but they will compete with each other to recruit all expected patients. The trial will be completed when the last newborn enrolled has completed the treatment schedule or achieved final retinal vascularization.

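### The condition for restarting at up to 0.3% tests the level measured on 0.2% against the 20 ng/mL safety ceiling itself, leaving no headroom for a dose increase of up to 1.5-fold

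*Protocol article*

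**What the plan says.** The protocol article, Stop criteria and dose changes, provides that after efficacy failure in the first stage "the study could be restarted increasing the concentration of propranolol eye drops solution up to 0.3" percent, on one exposure condition: "if plasma propranolol concentrations are below the cut off of 20 ng/ml". It gives no lower threshold, no margin and no projection to the new strength. It also does not say whether the condition applies to a mean or to every value.

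The levels available at that point are described under Data collection methods: "To investigate the safety of propranolol 0.2% eye micro-drops treatment, the concentration of propranolol will be measured on dried blood spots", at steady state on day 10, at 0, 2, 4 and 6 hours.

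The same 20 ng/mL appears in two other roles. Efficacy and safety of oral propranolol says that "it appears prudent to avoid in future clinical trials propranolol concentrations higher than 20 ng/mL". Experimental plan (text after Fig. 1) explains the value by "considering the serious adverse effects observed in newborns receiving oral propranolol with plasma concentrations around 20 ng/mL", and calls the eye drops safe "if the mean propranolol plasma concentration will be less than 20 ng/ml".

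**The concern.** A level measured on one dose says whether that dose is acceptable. To clear a higher dose, the level has to be projected to that dose before it is compared with the ceiling. Here the number that declares 0.2% safe also clears a strength up to half as high again. A cohort just under 20 ng/mL would satisfy the written check, and a new group of preterm infants could then be started on a strength expected to exceed the protocol's own cut-off.

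Continuous monitoring and the rule to stop treatment after a severe adverse event would still apply, but they act after exposure. This check is the one meant to act before it.

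**Working it through.** **How the clause is reached.** It applies after six or more failures in the first 37 infants (Experimental plan). I reproduced that design first. With failure rates of 19% and 9.5%, the probability of declaring the treatment effective is the sum over x = 0 to 5 of P(X1 = x) × P(X2 ≤ 12 − x), where X1 is binomial on 37 infants and X2 on the remaining 59. This gives 0.0493 at 19% and 0.802 at 9.5%, matching the stated alpha of 0.05 and power of 80%. The probability of six or more failures in 37 is 0.73 at 19%, 0.92 at the 24.5% from the second historical analysis, and 0.13 at 9.5%. If the drug does not work, the clause will probably be consulted.

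**Headroom.** Inputs: present strength 0.2% (Intervention), restart strength up to 0.3% and the 20 ng/mL condition (Stop criteria and dose changes). Drop number, volume and frequency are taken as unchanged. With r = new strength / 0.2% and levels assumed proportional to dose:

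- projected level = observed level × r
- highest observed level compatible with the ceiling = 20 / r

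| New strength | r | 20 / r (ng/mL) | Observed levels that pass as written but project to 20 or more | Projected range |
|---|---|---|---|---|
| 0.25% | 1.25 | 16.0 | 16.0 to 20 | 20 to 25 |
| 0.3% | 1.5 | 13.3 | 13.3 to 20 | 20 to 30 |

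**If levels are not proportional to dose.** If the level rises only 1.2-fold at 0.3%, the band is 20/1.2 = 16.7 to 20. If it rises 1.8-fold, the band is 20/1.8 = 11.1 to 20. Any rise above 1-fold leaves some band.

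**Mean or every value.** If the condition refers to the mean, a mean of 13.3 to 20 passes. If it refers to every value, a cohort whose highest value is 13.3 to 20 passes, although an infant with that exposure would project to 20 or more at 0.3%.

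**How likely is the band?** The article gives no measured level on 0.2%, and for 0.1% says only "consistently below the cut-off value of 20 ng/mL". As a rough assumption, take the same level per mg/kg as the oral drug, about 20 ng/mL at 1 mg/kg/day:

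- daily dose: 6 µL × 2 µg/µL × 3 drops × 4 times × 2 eyes = 288 µg
- per kg, at the mean birth weight of 843 g (Table 1): 0.288 / 0.843 = 0.342 mg/kg/day
- level on 0.2%: 0.342 × 20 = 6.8 ng/mL; on 0.3%: 6.83 × 1.5 = 10.2 ng/mL
- exposure per mg needed to reach 13.3 on 0.2%: 13.3 / 6.83 = 1.95 times oral

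Intervention prints 6 µg per micro-drop, but 6 µL of a 0.2% solution holds 12 µg, which is the figure used here. With the printed figure the estimates halve, to about 3.4 and 5.1 ng/mL.

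**The case against.** The strongest reply is that the band is unlikely to be entered. The article reports lower plasma levels with topical than with oral treatment, in rabbits and in newborns on 0.1%, and the tear duct is compressed to limit absorption. Infants are diagnosed at a mean of 34.2 weeks postmenstrual age and will usually weigh more than at birth. On the oral-equivalent assumption, 13.3 ng/mL would need a treatment weight near 433 g (0.288 / 0.433 = 0.665 mg/kg/day; × 20 = 13.3). The clause is also permissive: it allows a restart, and a smaller step, without requiring either. All of this stands and limits the practical weight. It does not repair the rule, whose purpose is to deal with levels that turn out higher than expected.

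A second reply is that an every-value check may already contain headroom. If the highest value is at least 1.5 times the mean, then all values below 20 force the mean below 13.3, and the projected mean stays below 20. That is correct as arithmetic, but it relies on a spread the article does not report. It also applies an every-value check while judging the result against a mean-based ceiling. Judged per infant, the gap remains.

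Third, the cut-off is approximate and proportionality is unproven, so 13.3 and 16.0 look more precise than they are. This is a fair caution about the exact limits, but an uncertain ceiling is no reason to use it without a margin.

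**Conclusion.** The concern holds. The condition for a higher strength is the safety ceiling applied to levels from the lower strength, and nothing in the article projects those levels forward. Under proportional exposure, observed levels of 13.3 to 20 ng/mL would clear a restart at 0.3% that projects to 20 to 30 ng/mL. The width of the band depends on proportionality; its existence requires only that exposure rises with concentration. The chance of a breach cannot be determined from the article, and what evidence there is points to low topical exposure. It should be fixed because it is a stated safety rule and the correction is cheap, but its practical weight is modest.

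**What to change.** Replace the condition in Stop criteria and dose changes with wording such as:

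> A restart at a concentration above 0.2% is permitted only if the day-10 level observed on 0.2%, multiplied by the ratio of the new concentration to 0.2%, is below 20 ng/mL.

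That means an observed level below 13.3 ng/mL for 0.3%, or below 16.0 ng/mL for 0.25%. Name the statistic in the same sentence: the mean, to match the safety criterion in Experimental plan, or a stricter choice such as each infant's highest day-10 value. If the number of drops changes too, use the ratio of total daily doses.

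The cost is one sentence in an amendment, applied to samples already planned. A restart at 0.3% may be permitted less often, or only at a smaller step such as 0.25%. If levels are as low as expected, the corrected check will pass and nothing is lost.
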